### Recruitment of participants

General practitioners, home care nursing services and nursing homes will be approached to support recruitment of patients and residents for the study. If interested, their staff will identify and screen candidate participants for eligibility. In the nursing home setting, all eligible residents will be invited to participate if they meet the inclusion criteria. General practitioners and nursing services will be asked to recruit each participant meeting the inclusion criteria until the recruitment goal is met. We will also approach potential participants through local newspapers, agencies, leaflets (e.g. in shops and pharmacies) and by word of mouth.

### Randomisation

Participants will be randomly assigned to either control or experimental group with a 1:1 allocation as per computer-generated randomisation schedule stratified by setting (community [primary care practice, nursing services] or nursing home). Participants will be randomly allocated via a telephone service provided by the Clinical Trial Centre at the University of Marburg (Koordinierungszentrum für klinische Studien [KKS]).

Research assistants will perform the data collection and examinations at baseline (T0) after 6 months of the intervention (T1) and after 12 months of follow up (T2). They will visit each participant either at their home or care home.

### Blinding

Blinding of participants is not possible due to the type of intervention. For practical reasons, study personnel cannot be blinded either, since at follow-up examinations participants are likely to communicate the study arm they have been allocated to. Moreover, assessments at baseline and follow-up of all participants, management of the intervention and other project tasks will be completed by the same members of the research team. A separation of tasks will not be possible. However, since randomisation will occur only after the baseline examination has been conducted, full concealment of allocation will be assured. In order to keep data collection at follow-up visits as unbiased and consistent as possible, a highly standardised protocol has been developed and will be implemented accordingly.

The study statistician will be blinded to participants’ allocation by being provided only pseudonymised data sets without explicit group allocation (only numbers will be used without revealing which was the intervention or control group).

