**Participant**				
Sociodemographic Data	Age, sex, level of care, family status, education level, ethnicity	X		
Physical Function	Short Physical Performance Battery	X	X	X
Quality of Life	EQ-5D-5L	X	X	X
Fear of Falling	Falls Efficacy Scale	X	X	X
Frailty	Clinical Frailty Scale	X	X	X
Cognitive Changes	Clock-drawing-test	X	X	X
Cognitive Impairment	Mini Mental Status Examination (MMSE)	X		
Walk Assessment	Number and duration of walks, assistance, type of assistance		X	X
Falls	Type and place of treatment		X	X
Treated Falls	Date, ICD Code, falls		X	X
Hospitalisation	Date of hospital admission and discharge, duration of hospitalisation, reason for hospitalisation (ICD-10-Code)		X	X
Death	Date of death, Reason for death (ICD-10-Code)		X	X

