#### Clock-drawing-test (to, T1, T2)

The Clock-drawing-test (CDT) is a useful tool in the clinical assessment of cognitive changes [24]. The CDT is a well-tolerated and accepted test completed by the participant [25].

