### Outcomes

We expect the intervention to impact upon muscle strength, balance and ability to walk. We therefore chose the Short Physical Performance Battery as the main outcome of the study. SPPB scores have been shown to be associated with disability in mobility and activities of daily living [26–28], future hospitalisation [29], health improvement [30] and mortality [30–32]. For these simple measures of performance, the SPPB shows a good reliability and validity [27].

As secondary outcomes we will evaluate quality of life (EQ-5D-5L), fear of falling (FES-I), physical activity (activity diary), cognitive executive function (clock drawing test), falls requiring medical attention, hospitalisation and death.

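### As written, the Blinding section leaves T1 and T2 clock-drawing scores open to rating bias, although coded drawings could be scored blind at the other centre

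*Protocol article*

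**What the plan says.** All references are to the protocol article.

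- **Blinding, first reason.** The section states that "study personnel cannot be blinded either, since at follow-up examinations participants are likely to communicate the study arm they have been allocated to".
- **Blinding, second reason.** It adds that, like the assessments of every participant before and after allocation, "management of the intervention and other project tasks will be completed by the same members of the research team. A separation of tasks will not" prove feasible. No outcome is exempted. The only role described as blinded is the study statistician, who receives pseudonymised data. For follow-up visits the stated safeguard is a standardised procedure. Randomisation takes place after the baseline examination.
- **Randomisation.** "Research assistants will perform the data collection and examinations at baseline (T0) after 6 months of the intervention (T1") and again at T2, on visits to the participant.
- **Table 1.** The "Clock-drawing-test" is listed at T0, T1 and T2.
- **Clock-drawing-test.** "The CDT is a well-tolerated and accepted test completed by the participant". The section names no rater, scoring scale or place of scoring.
- **Outcomes.** The secondary outcomes include "cognitive executive function (clock drawing test"). No other measure of this outcome is named.
- **Sample size.** The Marburg centre is to recruit 230 people from the community and the Witten centre 115 from nursing homes.

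**The concern.** The general rule puts every assessment in the hands of staff who know the allocation and also run the walking programme. For the SPPB and the interview-based measures this is hard to avoid, because the assessor must be with the participant. The clock-drawing test differs in one respect: it leaves a product that can be scored later by someone who never meets the participant.

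If the drawings are scored by staff who know the arm and manage the intervention, the T1 and T2 scores may drift in favour of walking. Blinding the statistician does not help, because the scores are already fixed when the data reach that person. A standardised procedure makes scoring more consistent but does not hide the arm. At stake is the credibility of the comparison on cognitive executive function, which is part of the effectiveness question under Aims.

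**Working it through.** **1. Does the rule reach the clock-drawing test?** Table 1 lists the test as an assessment at all three visits. The Randomisation section gives data collection at these visits to research assistants. The Blinding section says that the people who assess also manage the intervention and that tasks cannot be separated. Taken together, and with no exception stated, these sections leave no room for a blinded rater. This is an inference from a general rule, because the article nowhere says who scores the drawings.

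**2. Does each reason apply to scoring a drawing?**

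| Reason in the Blinding section | SPPB and interviews | Scoring a coded drawing afterwards |
|---|---|---|
| Participant reveals the arm at the visit | Applies | Does not apply: the scorer does not meet the participant |
| Same staff do all tasks | Applies | Applies within a centre; can be met by exchange between two centres with different participants |

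**3. How many scores are exposed?** Inputs from the Sample size section: 345 participants planned (230 + 115 = 345) and 40% expected loss during the 6 months to T1. The plan's own figure first: 345 × (1 − 0.40) = 207, which agrees with the 206 required for analysis.

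- T0: the test is done before randomisation, so no arm exists yet. These drawings are not exposed to arm-related bias, unless scoring is put off until after allocation, which the article does not suggest.
- T1 and T2, no loss: 345 × 2 = 690 drawings. This is the upper limit.
- T1 and T2 with 40% lost by T1 and no further loss: 207 × 2 = 414 drawings. Loss between T1 and T2 would lower this number.

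**4. How much could it matter?** The article gives no size for rater bias, so the following is an illustration on assumed values only. Let unblinded scoring shift the difference between arms by *b* residual standard deviations when there is no true effect. With *N* analysed in a 1:1 trial, e = b × √(N/4), and the type I error of a nominal two-sided 5% test is 1 − Φ(1.96 − e) + Φ(−1.96 − e).

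| Assumed b | N = 206 | N = 345 |
|---|---|---|
| 0 | 5.0% | 5.0% |
| 0.05 | 6.5% | 7.5% |
| 0.10 | 11.1% | 15.3% |
| 0.20 | 30.0% | 45.9% |

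For example, b = 0.10 and N = 206 give e = 0.10 × √51.5 = 0.718 and a type I error of 11.1%. The table shows that a small shift would be enough to matter. It does not show that any shift will occur.

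**The case against.** The strongest reply has four parts.

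- **The rater is not named.** The article does not say who scores the drawings, how, or even that they are on paper, and a fuller document may specify this. That stands as a limit. A reader might infer that the article states that intervention staff score the drawings; it does not. What it does state is a categorical rule with no exception, and blinded scoring would contradict that rule as written.
- **The second reason is a staffing constraint, and it is genuine.** The article gives no staffing by centre, and it does not say whether staff at one centre know the other's allocations. This also stands. The exchange works only if suitable scorers at the other centre do not know the allocations, which has to be checked.
- **Lack of blinding is already disclosed**, both in the Blinding section and as a limitation in the Discussion. That is true, and nothing in the article is contradictory here. But disclosure does not remove a bias that can be avoided for this one outcome.
- **The gain is narrow.** The test would still be given by unblinded staff to unblinded participants. That is correct: only bias in scoring is removed.

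A reader might also count all three visits, 345 × 3 = 1,035 drawings, as exposed. The timing of randomisation does not support this, because T0 comes before allocation.

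**Conclusion.** The point holds in a limited form. As written, the Blinding section rules out blinded rating for every assessment, including one whose scoring can be separated from the visit. Neither stated reason need prevent blind scoring of the clock drawings. The exposed scores are those at T1 and T2, at most 690 and about 414 under the planned loss.

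This rests on three assumptions: that the general rule covers scoring of the drawings, that the drawings are kept in a form that can be coded and copied, and that staff at the other centre can be kept unaware of the allocations. The size of the bias is unknown.

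It would be tempting to read this as a case against the unblinded assessment of the trial as a whole. The article does not support that: its reasons are sound for measures that need contact with the participant, and the primary outcome, the SPPB, is not touched by this point. The weight is that of a minor, inexpensive improvement to one secondary outcome.

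**What to change.** - Label each drawing with a code that shows neither arm nor visit.
- Exchange scans between the two centres. Have existing staff at the other centre, confirmed not to know those participants' allocation, score them.
- Score in mixed order across T0, T1 and T2. The T0 drawings are included to mask the visit and keep scoring consistent, not because they carry arm-related bias.
- Amend the Blinding section to say that clock-drawing scores are rated blind, while administration of the test, the SPPB and the other measures are not.

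**Cost.** Drawings must be scanned, coded and exchanged. The workload is uneven: Witten staff would score drawings from 230 participants and Marburg staff from 115, twice as many at Witten (230 / 115 = 2). If each drawing is scored once either way, the total number of ratings does not change. No extra visit or test is needed, and sample size and significance level stay as they are.

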### Study procedure and intervention

After baseline assessments (T0) and randomisation, individuals in the intervention group will participate in a supported physical activity intervention for 6 months. They will be visited by an assigned volunteer three times a week to go for a walk outdoors. The duration of the walk will depend on the participant’s physical ability. The aim is to gradually increase walking duration to three times 50 min to meet the WHO recommendation of 150 min per week [6]. In case of bad weather, the activity can take place indoors and will consist of exercises for balance and strength based on a programme of the federal centre for health education [15]. Each participant and his/her volunteer together will keep an activity diary, noting the date, time, duration and type of each activation exercise (outdoors or indoors). Events relevant for safety, e.g. falls or injuries, will also be recorded. Furthermore, after each walk, the subjectively experienced physical strain of the walk will document by a visual analogue scale.

Participants in the control group are invited to two lectures covering topics related healthy ageing during the 6 months of the intervention. The presentations will be in an easy to understand and entertaining manner and address health related topics for older people, e.g. nutrition. After 6 months of intervention the post intervention examination will take place (T1). We will evaluate the effect of the intervention in comparison with the control group. Study participants in both groups will be followed for another 6 months until the 12 months final examination (T2). During this period, the study centres will neither provide nor coordinate any walking service. However, we expect the collaborating partners and other community services to continue providing support for regular walking as initiated during the first 6 months of the study.

The evaluation of the extended period at T2 has two main objectives. First, to prolong participants’ follow-up and to assess long-term effects of regular walking (up to 12 months) and second, to evaluate potential sustainability and dissemination of the study intervention after cessation of support from the study centres (Fig. 1).

**Fig. 1 Fig1:**
[figure not shown]
Study Flowchart

### Measurements

#### Demographic data (T0)

To characterise the participants, we will collect the following sociodemographic data: age, sex, body weight and height, educational level, family status, ethnicity and care level if applicable.

#### Mini mental status examination (T0)

For detecting cognitive impairment, the Mini Mental Status Examination (MMSE) [14] is used to check eligibility and will only be performed at baseline [16]. It is a widely utilised tool designed as an interview with the participant assessing central cognitive functions.

#### Short physical performance battery (T0, T1, T2)

The Short Physical Performance Battery (SPPB) includes several supervised activity tests rating balance, gait speed and the ability to get up from a chair in form of an external assessment [13].

#### Quality of life (T0, T1, T2)

Quality of life will be assessed using the validated German version of the EQ-5D-5L questionnaire, developed by the EuroQol Group [17]. This tool provides a simple, generic measure of health-related quality of life for clinical and economic appraisal.

#### Falls efficacy scale (to, T1, T2)

We will use the Falls Efficacy Scale *(*FES-I) questionnaire [18, 19], which allows for a convenient measure of falls related self-efficacy with excellent reliability [20], validity [21] and sensitivity to change [22].

#### Frailty (T0, T1, T2)

Frailty will be measured with the Clinical Frailty Scale (CFS) [23], which is a quick and valid subjective assessment tool of frailty.

#### Clock-drawing-test (to, T1, T2)

The Clock-drawing-test (CDT) is a useful tool in the clinical assessment of cognitive changes [24]. The CDT is a well-tolerated and accepted test completed by the participant [25].

#### Physical activity record (T1, T2)

The participant states the number and duration of walks during the past 14 days and whether she/he walked together with a volunteer or somebody else.

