To our knowledge, so far only a few studies examined the effects of a walking intervention on community dwelling individuals. A British mixed-methods study examined a sample of people between 60 and 75 years who were recruited in primary care practices [9]. This complex intervention included feedback by pedo- and accelerometers, scheduled practice nurse consultations and activity diaries to establish regular self-paced walking. There was an improvement in the primary outcome “daily step-counts” and the participants reported gains in health and wellbeing in the qualitative component of the study [9]. However, the quantitative component lacked these and other health related measures to back up the qualitative findings (e.g. physical function, quality of life). Other major limitations of the study are the need for qualified staff and expensive technological equipment [9]. An Australian study on community dwelling individuals aged 65+ years evaluated a self-paced 48 week walking programme that involved mailed printed manuals and telephone coaching [10]. The intervention successfully led to an increase in activity and physical function as measured by the Short Physical Performance Battery. In addition, the sample was relatively fit and lacked older individuals with mild and moderate limitations [10]. Another pilot study showed that a combination of initial motivation by a peer volunteer and subsequent activity such as walking in groups, yoga or dancing led to behavioural changes in older people and improved physical activity [11].

Taken together, these studies show that interventions aimed at promoting regular walking improve older persons’ health. However, the interventions were complex and required professional input. Moreover, individuals who already had physical, sensory and/or cognitive limitations were not or not sufficiently included in the community dwelling studies.

The aim of the POWER Study is to investigate whether volunteer-supported outdoor-walking improves the physical function and quality of life of older people. A further aim is the implementation of the intervention in existing aid structures (e.g. regional health department). The POWER Study design has been conceptualised and piloted [12] as a simple and low-threshold intervention that is targeted at older people with inadequate activity levels, already present minor restrictions in physical and mental functioning preventing them from self-paced physical activity, and a lack of support.

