### Eligibility

Eligibility criteria will be assessed at baseline.

Inclusion criteria:
People aged ≥ 65 yearsReduced physical function (Short Physical Performance Battery Score (SPPB [13];)< 9 at baseline)Not confident to go for a walk on their own

Exclusion criteria:
Not giving informed consentMini-mental status examination (MMSE) score at baseline < 18 [14]Insufficient physical function to allow for volunteer-supported walking with adequate safety (SPPB at baseline ≤2 in nursing homes and ≤3 in the community setting)Excellent physical function making it improbable that participants will benefit from the intervention (SPPB-Score ≥10)Permanently bedriddenCan only be mobilised in a wheelchairRegular physical activity levels at least equivalent to the intervention (> 150 min/week)Life expectancy of less than 6 monthsOther foreseeable inability to take part in the intervention for 6 monthsKnown alcohol or drug addiction or active psychosis during the last 12 monthsAnother person of the same household participating in the study

Individuals using a walking frame, a cane or a wheeled walker will be included, as well as those suffering from Parkinson’s disease or mild cognitive impairment (MMSE ≥18). We expect all of these to benefit from the intervention, and we presume that volunteers will be able to cope with these disabilities or restrictions.

Eligibility criteria will be communicated to recruiting organisations, such as nursing homes or primary care practices. The final decision regarding eligibility will be made at the baseline examination, since some in- or exclusion criteria are formally assessed on this occasion, such as cognitive or physical function.

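### Physical activity is a secondary outcome and an exclusion criterion, yet no activity measure is scheduled at baseline, so the outcome cannot be baseline-adjusted

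*Protocol article*

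**What the plan says.** All references are to the protocol article.

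- **Eligibility.** "Eligibility criteria will be assessed at baseline". One exclusion is numeric: regular activity above 150 minutes a week. The section adds that "some in- or exclusion criteria are formally assessed on this occasion, such as cognitive or physical function"; activity is not among the examples.
- **Recruitment of participants.** At the recruiting organisations, "their staff will identify and screen candidate participants for eligibility".
- **Measurements.** The participant-reported activity measure has the heading "Physical activity record (T1, T2"). In it, "The participant states the number and duration of walks during the past 14 days" and says whether someone walked along.
- **Table 1.** The Walk Assessment row ("Number and duration of walks, assistance, type of assistance") is marked at T1 and T2 and blank at T0. SPPB, EQ-5D-5L, the Falls Efficacy Scale, the Clinical Frailty Scale and the clock-drawing test are marked at all three times.
- **Mini mental status examination.** This test "is used to check eligibility and will only be performed at baseline", so one instrument is scheduled at T0 purely for eligibility.
- **Aims, Outcomes and Data analysis.** General physical activity is part of the effectiveness question and a secondary outcome, with the activity diary named as its instrument. Secondary outcomes are to be analysed by ANCOVA, t-test or Mann-Whitney test. The amount of physical activity is also given as a reason for the mediator analysis of falls.
- **Study procedure and intervention.** The diary is kept jointly by the participant and the assigned volunteer during the intervention.

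**The concern.** The text and Table 1 agree that the activity record starts at T1. This is a stated scheduling choice, not a detail that a condensed article has left out. It has four consequences.

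1. An ANCOVA of activity adjusted for its own baseline is ruled out, although the plan relies on that kind of adjustment for SPPB and lists ANCOVA for secondary outcomes.
2. Starting activity cannot be compared between the arms.
3. The mediator analysis lacks a prior value for one of the two variables it names. The level of a mediator is not randomised, so earlier activity is an obvious candidate confounder of the path from activity to falls. Fear of falling has a T0 value; activity does not.
4. The Background describes the intervention as "targeted at older people with inadequate activity levels, already present minor restrictions in physical and mental functioning", but the measures shown cannot describe how active the enrolled participants were at entry.

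T0 is the only time at which this can be put right. Randomisation follows the baseline examination, and afterwards participants and assessors know the allocation.

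**Working it through.** **Step 1: the plan's own figure.** The sample size section concerns SPPB, which has a T0 value. Inputs: difference 1 point (standard deviation of the two means 0.50), within-group SD 2.8, covariate R-square 0.5, two-sided 5% level, 95% power.

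- Adjusted SD = 2.8 × √(1 − 0.5) = 1.98.
- Noncentrality at 103 per arm = 206 × (0.5/1.98)² ≈ 13.1. The noncentral F test with one covariate gives 95.03% power; 102 per arm gives 94.84%. The stated 103 per group reproduces.
- 206/(1 − 0.40) = 343.3, so 344, against 345 stated; 345 × 0.6 = 207. This agrees within rounding.

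Nothing in this point alters those figures.

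**Step 2: which measures exist at T0.**

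| Item | Role | T0 instrument shown? |
|---|---|---|
| SPPB | entry criterion and primary outcome | yes |
| MMSE | entry criterion | yes |
| EQ-5D-5L, Falls Efficacy Scale, clock-drawing test | secondary outcomes | yes |
| 14-day walk record | the only activity measure shown for both arms | no (T1, T2) |
| Activity diary | instrument named for the activity outcome | no; kept with the volunteer after randomisation, so intervention arm only |

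Neither activity instrument gives a T0 value. As described, the diary cannot support a comparison between arms at any time, because controls have no volunteer. That leaves the 14-day record as the usable outcome measure.

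**Step 3: precision lost without a baseline value.** The document gives no correlation for activity, so r = 0.4 to 0.6 is an assumption. Adjusting for a baseline with correlation r to follow-up multiplies the outcome variance by (1 − r²).

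| r | Variance reduction r² | Equivalent gain in participants, 1/(1 − r²) − 1 |
|---|---|---|
| 0.4 | 0.16 (16%) | 1/0.84 − 1 = 19% |
| 0.6 | 0.36 (36%) | 1/0.64 − 1 = 56% |

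**Step 4: the same loss as power.** Assume, for illustration only, that activity had the standardised effect planned for SPPB (1/2.8 = 0.36) with 103 per arm. Power without a covariate is 72%. With a baseline covariate it is 77% at R-square 0.10, 84% at 0.25, 91% at 0.40 and 95% at 0.50. The document gives no effect size, SD or R-square for activity, so these figures show direction and rough scale only.

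**The case against.** Three stronger readings are tempting, and the document supports none of them.

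- *The activity criterion rests on an unrecorded judgement, so active people who enter could never be identified.* The article does not say how the criterion is ascertained or filed. Life expectancy, addiction and lack of confidence to walk alone also have no row in Table 1, and a screening form may well exist; an article commonly leaves that to the full protocol. Pre-screening by staff, the SPPB ceiling and the confidence criterion also limit the entry of active people. What stands is narrower: no T0 instrument for this criterion is shown, whereas SPPB and MMSE have one.
- *The missing baseline biases the between-arm difference.* It does not. Under 1:1 randomisation, chance imbalance is already allowed for in the standard error, and the t-test and Mann-Whitney test that the plan also lists need no baseline. The cost is precision and a balance check.
- *Lack of support, part of the target description, also needs a T0 measure.* It describes the target group and is not an entry criterion. Family status and care level at T0 partly cover it.

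Two further objections carry some weight. The gain depends on an assumed correlation: entry criteria restrict the range of starting activity, which may lower r, and other T0 variables such as SPPB or fear of falling could recover part of the precision. Also, the record covers walks only, while the exclusion concerns all regular activity, so moving the record to T0 unchanged would not by itself document the criterion.

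**Conclusion.** The point holds in a limited form. Activity is an effectiveness question, a secondary outcome and part of the mediator analysis, yet the document schedules no activity measure at T0. The outcome cannot be adjusted for its own baseline or checked for starting balance, the mediator analysis has no prior activity value, and no T0 instrument is shown for the 150-minute exclusion. The loss is precision, about 19% to 56% in equivalent participants for this one outcome if r lies between 0.4 and 0.6, together with a weaker description of who was enrolled. The upper part of that range is less likely if the entry criteria narrow the spread of baseline activity or if other T0 covariates are used. How many people above the threshold might enter cannot be told from the document.

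The primary outcome and its sample size are unaffected. The sections on the diary, the activity record and the outcomes must also be reconciled, because the named outcome instrument is described for one arm only.

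**What to change.** 1. Schedule the 14-day record at T0, before randomisation, in the section on the physical activity record and in the Walk Assessment row of Table 1.
2. Add an item on other regular activity. The 14-day walking total divided by 2, plus other regular activity per week, then gives minutes per week and can document the existing exclusion. If the outcome is meant to be all activity and not walking alone, keep the item at T1 and T2 as well.
3. Use the T0 value as covariate for physical activity at T1 and T2, and make it available to the mediator analysis.
4. In the Outcomes section, name this record as the between-arm instrument in place of the activity diary. The diary can still describe what was delivered in the intervention arm.

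The cost is a few minutes of added burden with an existing questionnaire at a visit that already takes place. The sample size and the primary analysis do not change.
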